##### Estimated sample size for objective 1b--inappropriate screening

We do not have estimates of the percentage of catheterized patients who are screened for ABU. We have based our estimates of the sample size on detecting a reduction in the intervention group of 25% in the percentage of catheterized patients who are screened for ABU. Based on estimates of the number of catheterized patients at Houston and San Antonio in a one-year time period (1,867 and 1,512, respectively), we will have 80% power to detect a 25% reduction in percentage of patients screened, even if the percentage of screened patients is as low as 10%.

#### Analyses for objective 1

For the analysis of inappropriate treatment, we will test for differences in the proportion of inappropriately treated episodes of bacteriuria between intervention and control sites using a hierarchical regression approach. Episodes will be nested within patients and patients nested within provider. Independent variables will be those described above. A significant value for the parameter estimate for the intervention will indicate that the audit feedback group differed from the control group.

For the analysis of inappropriate screening, we will conduct a logistical regression analysis in which the dependent variable will be whether or not the catheterized patient received screening for ABU. Hierarchical models will allow nesting of patients within provider. An indicator variable for the intervention effect will be used to determine differences between the audit feedback and control groups. Independent variables will include variables to indicate the unit in which the patient was hospitalized in addition to patient-related characteristics. A similar logistical analysis will be run for the secondary outcome of whether or not the hospitalized patient had a urinary catheter. For both the primary and secondary outcomes, the number of cultures per 100 device-days and the number of device-days per 100 bed-days will be compared among the units using analysis of covariance.

For the secondary outcome of days of inappropriate antibiotic use, we will first examine the distribution of the number of days that antibiotics were given. If the distribution is not normally distributed, we will consider appropriate transformations. In addition, we may consider use of hierarchical Poisson regression models.

For the remaining dependent variables identified in Table 3, when possible, we will test for differences between the intervention and control using the hierarchical regression approaches above. For rare outcomes for which fewer than 10 total cases are expected, we may be unable to conduct comparative analyses and will instead provide descriptive analyses.

#### Analysis plan and sample size for objective 2

We expect to survey 100 providers at the MEDVAMC in year 2, 100 providers at the MEDVAMC in year 3, and 100 providers at the STVHCS in year 3, resulting in 300 paired pre/post surveys. We will calculate the raw number and proportion of providers at each site whose survey responses exhibit clinically meaningful change (provider learning), as described in Table 2. Though we recognize that this measurement process will be exploratory, we expect the results to shed light on the efficacy of the intervention from a provider perspective, triangulating with improved clinical outcomes from objective 1 and thus augmenting our overall rationale for dissemination. We also intend to explore which of the attributes measured in objective 2 are associated most strongly with changes in clinical outcomes measured in objective 1 and to assess how well any empirical relationships are supported conceptually. Finally, we will assess the empirical relationships between provider learning and provider demographics.

To measure the success of the audit and feedback system, we will document how many episodes of bacteriuria were audited (underwent medical-record review), how many audited episodes resulted in feedback (a phone call or visit to the provider), and how many episodes of feedback were delivered to the correct provider (someone directly involved in the prescribing decisions for the patient). The information about correct delivery of feedback will be particularly important, and we expect the majority of the application barriers to occur in this area. This assessment will be made every three months by the research coordinator. If fewer than 90% of episodes of bacteriuria receive audit, or if fewer than 80% of audits are delivered to the correct team within three days, we will reassess our audit and feedback methods. These evaluation elements will be critical for developing implementation and dissemination protocols.

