#### Healthcare providers targeted in the intervention

The audit and feedback intervention will be applied to the healthcare providers who make the decision to treat CAUTI. The healthcare provider who makes the decision to order a urine culture and to prescribe antibiotics for a positive urine culture differs depending on hospital unit. In the internal-medicine wards, this decision is made by internal-medicine residents, who are usually either interns or second-year residents (postgraduate year 1 or 2). Approximately 170 medical residents rotate through the intervention site medicine wards per year. The extended-care units are staffed by nurse practitioners and physician assistants, with supervision provided by VA staff physicians trained in geriatrics. Therefore, in the extended-care ward, the intervention will target the nurse practitioners, physician assistants, and staff physicians, currently 17 individuals.

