### Analysis

#### Analysis plan and sample size for objective 1

##### Independent variables for objective 1

For the variables in objective 1, it is important to understand that the intervention is applied to the healthcare providers, but the unit of analysis for the outcomes is episodes of bacteriuria occurring in catheterized inpatients (Table 3). We will account for the correlation that may exist among patients treated by the same healthcare provider in our regression models. The independent variables include age and gender of the patient, duration of catheter use, catheter type, hospital ward and service, types and quantities of organisms found in the urine, number of white blood cells (WBCs) in urine, number of WBCs in the serum, and highest temperature in 24 hours around the time of urine specimen collection.

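### The 80% power for objective 1b carries no allowance for provider clustering, although the planned test nests about 10 patients within each provider

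*Protocol article*

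**What the plan says.** The sample-size section for objective 1b says that the screening percentage is not known and that the calculation rests on "detecting a reduction in the intervention group of 25% in the percentage of catheterized patients who are screened for ABU". Its inputs are "estimates of the number of catheterized patients at Houston and San Antonio in a one-year time period (1,867 and 1,512, respectively"). Its conclusion, with 10% named as the floor, is "we will have 80% power to detect a 25% reduction in percentage of patients screened, even if the percentage of screened patients is as low". It gives no alpha, sidedness, ICC or design effect. The neighbouring section for objective 1a names a two-sided 0.05 test of two independent proportions.

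The section Analyses for objective 1 plans a logistic regression of whether each catheterised patient was screened, and adds: "Hierarchical models will allow nesting of patients within provider". The section on independent variables for objective 1 says: "We will account for the correlation that may exist among patients treated by the same healthcare provider in our regression models".

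On the number of providers, the section on healthcare providers targeted says: "Approximately 170 medical residents rotate through the intervention site medicine wards per year". It adds 17 individuals in extended care. The Setting section explains that providers at the two sites should not overlap.

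**The concern.** The power figure and the planned test assume different things about the data. The figure rests on counts of patients. The test allows patients of the same provider to resemble one another. Each provider works at one site and therefore in one arm, so any positive within-provider correlation increases the variance of the intervention term and lowers power. Some correlation is to be expected, because ordering a urine culture is the provider's own decision and is the behaviour the intervention targets.

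Screening is one of the two named hypotheses under objective 1 and stands second in Table 3. If the screening rate proves low and the 1b comparison is null, a reader relying on the stated power could take the result as evidence against a 25% reduction when the planned comparison had less power than claimed.

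**Working it through.** **Inputs from the article.** Control n = 1,512; intervention n = 1,867; screening rate 10%; reduction 25%, read as relative because a fall of 25 percentage points from 10% is impossible. Intervention-site providers: 170 + 17 = 187, so m = 1,867 / 187 = 9.98 patients per provider per year.

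**Assumptions, not in the article.** The ICC; the same m at the control site; equal cluster sizes; alpha 0.05 for 1b (stated only for 1a).

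**Step 1: the stated figure.** Two-proportion z-test with independent patients:

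power = Φ[(p1 − p2 − z × SE0) / SE1]

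For 10% v 7.5%, the pooled proportion is (1,512 × 0.10 + 1,867 × 0.075) / 3,379 = 0.0862. This gives SE0 (pooled) = 0.00971 and SE1 (unpooled) = 0.00983.

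- One-sided, z = 1.645: (0.025 − 0.01597) / 0.00983 = 0.918, power 82.1%. The unpooled version gives 81.5% and the continuity-corrected version 80.4%.
- Two-sided, z = 1.960: (0.025 − 0.01903) / 0.00983 = 0.607, power 72.8%.
- 10% taken as the reduced rate (13.3% v 10%), two-sided: 85.3%.

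The stated 80% is therefore what a calculation with independent patients gives one-sided. It is also met, with a few points to spare, if 10% is the reduced rate. Neither leaves much room for a design effect.

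**Step 2: add provider clustering.** Design effect DE = 1 + (m − 1) × ICC; both counts are divided by DE and step 1 is repeated. At ICC 0.05, DE = 1 + 8.98 × 0.05 = 1.45, and the effective counts are 1,043 and 1,288.

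| ICC | DE | 10% v 7.5%, one-sided | 10% v 7.5%, two-sided | 13.3% v 10%, two-sided |
|---|---|---|---|---|
| 0 | 1.00 | 82.1% | 72.8% | 85.3% |
| 0.01 | 1.09 | 79.1% | 69.1% | 82.2% |
| 0.02 | 1.18 | 76.3% | 65.7% | 79.2% |
| 0.05 | 1.45 | 68.7% | 57.0% | 70.6% |
| 0.10 | 1.90 | 58.7% | 46.4% | 59.1% |

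Each column should be read downwards from its own ICC 0 value. At ICC 0.05 clustering costs 13.4, 15.8 and 14.7 points respectively.

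**Step 3: how much slack there is.** Power falls below 80% once the ICC exceeds about 0.007 (10% v 7.5%, one-sided) or about 0.017 (13.3% v 10%, two-sided). For 10% v 7.5% two-sided it is below 80% with no clustering at all.

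**Step 4: what 80% two-sided power would need.**

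| ICC | Control rate needed for a 25% reduction | Reduction detectable from 10% |
|---|---|---|
| 0 | 11.7% | 27% |
| 0.01 | 12.7% | 28% |
| 0.02 | 13.6% | 29% |
| 0.05 | 16.3% | 32% |
| 0.10 | 20.4% | 36% |

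**Step 5: sensitivity to the unknown control-site cluster size.** At ICC 0.05, with about 10 patients per provider at the intervention site and 5 to 20 at the control site, power for 10% v 7.5% runs from about 61% down to 50% two-sided and from about 73% down to 62% one-sided.

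**Step 6: pooling Years 2 and 3.** With both counts doubled, ICC 0.05 and 10% v 7.5% two-sided, power is about 85% if Year 3 brings entirely new providers (DE 1.45). It is about 74% if the same providers continue (m about 20, DE = 1 + 18.97 × 0.05 = 1.95).

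**The case against.** The strongest reply is that the size of the loss depends on an ICC the article does not give. At 0.01 the one-sided figure is still 79% and the 13.3% v 10% figure is 82%, and nothing in the document favours 0.05 over 0.01. The model also adjusts for hospital unit and patient characteristics, so the relevant ICC is a conditional one and may be smaller than a crude one. This stands, and it is why a range is shown and no single value is put forward.

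Second, a reader might infer that clustering takes the stated 80% down to 57%. The documents do not support that. The 57% is two-sided, and the two-sided figure is already 73% with independent patients. Nor should 57% and 71% be joined into one range, since they belong to different readings of the 10%.

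Third, a reader might infer that objective 1b is underpowered in general. That does not follow either. The article offers 10% as a low extreme for an unknown rate. At a 20% rate and a design effect of 1.45, two-sided power is about 89%.

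Fourth, an article may leave an ICC to the full protocol. That would be fair if the article gave no power figure. Here it prints both a definite figure and an analysis with a different variance, and the mismatch is visible in its own text.

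**Conclusion.** The point holds in a limited form. The 80% stated for objective 1b at a screening rate as low as 10% fits independent patients and does not describe the provider-nested model that the article plans. The claim has almost no slack: an ICC of about 0.01 to 0.02 is enough to bring it below 80% under either reading that meets the figure without clustering, and an ICC of 0.05 would bring it to about 69% or 71%. The unstated alpha and sidedness for 1b are a separate matter, and the 73% two-sided value at ICC 0 belongs there.

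This rests on about 10 patients per provider at the intervention site, which follows from the article's counts, and on an assumed ICC, an assumed equal cluster size at the control site and equal clusters, which do not. How the authors obtained 80% is not documented; that clustering was left out is inferred from the match in step 1 and from the independent-proportions basis stated for 1a.

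The point is specific to 1b. At 300 episodes per site, objective 1a has about 300 / 187 = 1.6 episodes per provider. With ICC 0.05 the design effect is 1.03 and power moves only from 83.6% to 82.5%.

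**What to change.** Restate the 1b power for the provider-nested model. Give alpha and sidedness, and say whether 10% is the control rate or the reduced rate. Divide both counts by 1 + (m − 1) × ICC, with m about 10 at the intervention site, the control-site value added, and an ICC estimated from the Year 1 surveillance already under way. Show a range of ICCs.

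Then either replace the 10% floor with the control rate that gives 80% power (two-sided: about 12.7% at ICC 0.01, 13.6% at 0.02, 16.3% at 0.05), or keep 10% and state the detectable relative reduction (about 28%, 29% and 32%). If Years 2 and 3 will be pooled for the test, say so and let the cluster size reflect providers who appear in both years.

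The cost is one recalculation and a reworded paragraph, with a less favourable stated figure. Surveillance already covers all patients on the study wards, so no extra patients and no change in procedures are needed.

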##### Estimated sample size for objective 1a--inappropriate treatment

We have estimated the sample size of episodes of bacteriuria needed at each of the two sites based on testing the differences in two independent proportions. The effect size to be detected is *h *= | φ_1 _- φ_2 _|, where φ = 2 arcsine √P [39]. Preliminary analyses found that the percentage of patients who received inappropriate treatment was 36%. Assuming a two-sided test, α = .05, and power of 80%, a sample size of 300 episodes is needed at each site in order to detect an 11% reduction in inappropriate treatment at the intervention site (down to 25%) compared to the control site rate of 36%. Specifically, *p*_1 _= .36, φ_1 _= 1.287, *p*_2 _= .25, φ_2 _= 1.047, and *h *= .24, which represent a small effect size. On the specific hospital units targeted in this study, there were over 3,000 discharges associated with urinary catheterization from the study wards at the two sites combined in fiscal year (FY) 2008. Thus, we should have adequate power to detect differences between the intervention and control sites. For the medicine units alone, we will have enough power to detect whether there was a difference in inappropriate treatment between intervention and control sites because there were approximately 1,600 patients at the Houston site estimated to have had catheters in the non-ICU medical bed sections in FY2008 and 1,300 unique patients in San Antonio.

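### Objective 1b: at a 10% control screening rate the stated patient numbers give about 73% power with a two-sided 5% test, not 80%, and the power statement leaves alpha, sidedness and the meaning of the 10% open

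*Protocol article*

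**What the plan says.** The section on the estimated sample size for objective 1b admits that no estimate of the screening percentage is available. It bases the calculation on "detecting a reduction in the intervention group of 25% in the percentage of catheterized patients who are screened for ABU". The counts are those for "Houston and San Antonio in a one-year time period (1,867 and 1,512, respectively"). From these it concludes that "we will have 80% power to detect a 25% reduction in percentage of patients screened". The same sentence then extends the claim to an unfavourable case, with the words "even if the percentage of screened patients is as low as 10" per cent.

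That section gives no significance level, no sidedness and no formula. The only test specification in the article is in the section before it, for objective 1a. There the sample size is "based on testing the differences in two independent proportions", with the arcsine effect size h, and the settings are introduced by "Assuming a two-sided test, α = .05, and power of 80" per cent.

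For the 1b analysis itself, the section Analyses for objective 1 plans a logistic regression with an indicator for the intervention and adds: "Hierarchical models will allow nesting of patients within provider".

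**The concern.** The 1b sentence supplies both patient numbers, the relative reduction and the lowest screening rate, so the power can be recalculated once a test is assumed. With the test specified one section earlier, the result falls clearly below 80%.

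Objective 1b is one of the two hypotheses under the first primary objective, and screening ranks second among the clinical outcomes in Table 3. Because the screening rate is unknown, the 10% clause carries the claim that the study is large enough even in an unfavourable case. If power there is 73%, the chance of missing a true 25% relative reduction is 27% rather than 20%.

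**Working it through.** **Inputs from the 1b section.** Intervention site (Houston) 1,867 patients; control site (San Antonio) 1,512; reduction 25%; screening rate 10%. The reduction has to be relative, since 25 percentage points cannot be taken from 10%. With 10% as the unreduced rate, the contrast is 0.10 against 0.75 × 0.10 = 0.075.

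**Inputs carried over from the 1a section (an assumption).** Two independent proportions, two-sided α = 0.05, h = |φ1 − φ2| with φ = 2 arcsine √p.

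**Check of the method on the article's own 1a figure.** For 0.36 against 0.25, h = 0.2398, and n per site = 2 × ((1.960 + 0.842)/0.2398)² ≈ 273. The pooled formula gives 274, and 292 with continuity correction. The stated 300 per site is therefore enough under a two-sided test, with 83% to 84% power. A one-sided calculation would need only 215. The 1a figure fits two-sided practice.

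**Objective 1b, arcsine, two-sided 5%.**
- φ(0.10) = 0.6435 and φ(0.075) = 0.5548, so h = 0.0887.
- Standard error = √(1/1,867 + 1/1,512) = 0.0346.
- z = 0.0887/0.0346 = 2.563.
- Power = Φ(2.563 − 1.960) = Φ(0.603) = 72.7%.

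**Same contrast and counts, other formulas.**

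| Formula | Two-sided 5% | One-sided 5% |
|---|---|---|
| Arcsine | 72.7% | 82.1% |
| Pooled z | 72.8% | 82.1% |
| Unpooled z | 72.0% | 81.5% |
| Log-odds Wald | 72.8% | 82.2% |
| Continuity-corrected | 70.8% | 80.4% |

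Exchanging the two site counts gives 70% to 73% two-sided. Even 1,867 patients at both sites would give only about 77%.

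**Other readings of the 10%, two-sided 5%, same counts.**
- Overall rate of both sites: solve (1,867 × 0.75p + 1,512 × p)/3,379 = 0.10, so p = 337.9/2,912.25 = 0.116. The contrast is 11.6% against 8.7%, h = 0.0963, z = 2.783, and power is 79.5%.
- Rate after the reduction: 13.3% against 10%, h = 0.1041, z = 3.008, and power is 85%.

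**What 80% two-sided power would need.** At the stated counts, either a control rate of about 11.7%, or a relative reduction of about 27% at 10% (27% gives 79.5%). At 10% against 7.5%, it would take about 2,005 patients per site with equal numbers. At higher control rates the stated counts suffice: power is 81% at 12%, 90% at 15% and 97% at 20%.

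All these figures treat patients as independent.

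**The case against.** The strongest reply is that the 1b text never says two-sided and never says whose rate the 10% is. That is correct. A reader might infer that the authors used a one-sided test, or that 80% can be reached in no other way. The article does not support that. A one-sided test does give 80% to 82%, but a two-sided test gives 79.5% if 10% is the overall rate and 85% if it is the reduced rate. Both readings are less natural than the unreduced rate: the 25% is described as a reduction in the intervention group, and the unknown quantity is the percentage from which it is taken. They are still possible, so the origin of the 80% remains unknown.

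It can also be said that the 10% is a floor and not a planning value, that power passes 80% from about 11.7% upward, and that surveillance covers all patients on the study wards with no recruitment target for 1b. This stands and limits the practical weight. Two years of patients would give about 95%, but the sentence rests on one year, and the third year delivers a different form of feedback.

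A reader might go further and put the true power well below 73% because patients are nested within provider, or because the design is pre/post. Positive correlation within provider would lower power, but the article gives no value for it, so no particular figure can be attached. Whether 1b should be tested as a difference in change between sites is a separate design question. Neither is needed for the point made here.

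**Conclusion.** On the natural reading, the stated 80% does not follow from the stated inputs. Power is about 73% (71% to 73% across formulas), about 7 percentage points lower. This rests on three assumptions: 10% is the control rate, the two-sided 5% test of objective 1a also applies to 1b, and patients are independent. Other readings come close to or exceed 80%, so the firm conclusion has two parts: the figure is not reproduced on the natural reading, and the text does not fix what is needed to say how it arose. The shortfall is confined to control screening rates below about 11.7%. It alters no sample size and leaves the 1a calculation untouched.

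**What to change.** Restate the sentence along these lines: with 1,867 and 1,512 patients and a two-sided 5% test, power to detect a 25% relative reduction is about 73% if the control screening rate is 10%; 80% power requires a control rate of about 12%, or a relative reduction of about 27% at 10%; these figures assume independent patients and make no allowance for the planned nesting within provider.

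State alpha and sidedness for objective 1b, and which group's rate the 10% is. If a one-sided test or another meaning of the 10% was intended, say so and give the figure on that basis. Baseline surveillance is already under way at both sites, so replace the assumed 10% with the year-1 screening rate once it is known and recompute.

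No extra patients are needed. The only cost is a slightly less favourable stated figure.

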**Methods/Design:**

The study uses a controlled pre/post design to test an intervention using audit and feedback of healthcare providers to improve their compliance with ABU guidelines. The intervention and the control sites are two VA hospitals. For objective 1 we will review medical records to measure the clinical outcomes of inappropriate screening for and treatment of catheter-associated ABU. For objective 2 we will survey providers' knowledge and attitudes. Three phases of our protocol are proposed: the first 12-month phase will involve observation of the baseline incidence of inappropriate screening for and treatment of ABU at both sites. This surveillance for clinical outcomes will continue at both sites throughout the study. Phase 2 consists of 12 months of individualized audit and feedback at the intervention site and guidelines distribution at both sites. The third phase, also over 12 months, will provide unit-level feedback at the intervention site to assess sustainability. Healthcare providers at the intervention site during phase 2 and at both sites during phase 3 will complete pre/post surveys of awareness and familiarity (knowledge), as well as of acceptance and outcome expectancy (attitudes) regarding the relevant practice guidelines.

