## Methods

### Study design

The study uses a controlled pre/post design to test an intervention using audit and feedback of healthcare providers to improve their compliance with ABU guidelines. The intervention and the control sites are two different VA hospitals.

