The intervention will begin in year 2. We will distribute guidelines and definitions concerning ABU and CAUTI at both sites in the form of a diagnostic algorithm. Guideline distribution to providers will continue at appropriate intervals at both sites for the ensuing two years. During the second year, we will provide individualized audit and feedback at the intervention site. The research team will review episodes of bacteriuria and the management implemented by the provider who ordered the urine culture. Research personnel will then visit the provider to discuss whether his or her behavior was or was not in compliance with ABU guidelines. Unit-level feedback will also be given by the research assistant on a monthly basis by presenting the unit's results in graphical form. The unit in this case will be the five hospital wards for the long-term care patients and the eight internal medicine teams for the medicine wards. At the control site, algorithm distribution alone will occur during the second year. During the second year, we will also evaluate the effect of the intervention on the barriers to guidelines implementation in terms of awareness, familiarity, acceptance, and outcome expectancy through pre/post surveys completed by healthcare providers at the intervention site. Exit (qualitative) interviews with study participants will also address potential barriers to implementation of our intervention protocol.

During the third year of the study, the individualized visits to providers will cease, but unit-level feedback will continue over the course of the third year at the intervention site. During this year, the surveys will be administered at the control site in addition to the intervention site so that we can assess the effect that the surveys alone have on prescribing behavior and on responses to survey questions. The purpose of the third year is to continue to measure elements of the study, as well as to evaluate issues of sustainability and the minimal intervention elements needed for dissemination.

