### Setting and participants

#### Setting

The intervention site and the control sites were chosen because they are alike in terms of ward organization, patient population, infection-control software, and clinician and medical resident involvement in patient care. We also studied the organizational context of the proposed intervention site (MEDVAMC) and control site (STVHCS) using the results of the VA Clinical Practice Organizational Survey (CPOS), Chief of Staff Module, with specific focus on responses to survey elements concerning support for guideline adherence and implementation of quality improvement measures [27]. Overall, the two sites are similar in several key elements relevant to our project. In particular, audit and feedback is not used extensively at either site and is primarily applied to clinicians' laboratory test ordering. Both sites rely on designated site champions to implement clinical guidelines or performance measures, although finding someone willing to take on this role was difficult at one of these sites because of time constraints. The leaders at both sites are strongly committed to continual improvement.

We believe that a hospital-wide intervention will be necessary (as opposed to intervening at the ward level) because medical residents travel throughout the hospital via consult services and thus, may potentially serve to diffuse knowledge throughout the facility. Hospital units at the intervention site with the highest rates of guideline-noncompliant behavior were identified, including the five general medicine wards and the five extended-care units, where 36.1% of patients received inappropriate treatment. The corresponding units at the control site have been selected for our study (three medicine wards and two extended-care wards). The intervention and control facilities are in different Veterans Integrated Service Networks, or VISNs, which is advantageous for study purposes. For the STVHCS to be a true control, healthcare providers should not overlap or have significant work-related communication with the intervention facility. Also, performing the study in two different VISNs will ultimately facilitate diffusion of the study intervention.

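### The tests for objectives 1a and 1b are stated as one contrast between two hospitals with no period or site-by-period term, although the design is controlled pre/post

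*Protocol article*

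**What the plan says.** The Study design section states: "The study uses a controlled pre/post design to test an intervention using audit and feedback of healthcare providers". The abstract adds that "the first 12-month phase will involve observation of the baseline incidence of inappropriate screening for and treatment of ABU at both sites", and Table 1 continues surveillance at both sites through years 2 and 3.

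Under Analyses for objective 1, the 1a test is described so: "we will test for differences in the proportion of inappropriately treated episodes of bacteriuria between intervention and control sites using a hierarchical regression approach". Its decision rule reads: "A significant value for the parameter estimate for the intervention will indicate that the audit feedback group differed from the control group". For 1b: "An indicator variable for the intervention effect will be used to determine differences between the audit feedback and control groups".

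The 1a covariate list begins: "The independent variables include age and gender of the patient, duration of catheter use, catheter type, hospital ward and service". It goes on to urine organisms, white cell counts and temperature. The 1b model adds unit indicators and patient characteristics. Neither list contains year, period, a baseline rate or a site-by-period term. The remaining Table 3 outcomes follow the same approach where possible.

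The 1a sample size treats the sites as two independent proportions, 36% for control and 25% for intervention. On ward selection, the Setting section says: "Hospital units at the intervention site with the highest rates of guideline-noncompliant behavior were identified". It gives 36.1% inappropriate treatment for those units. The control wards are the corresponding units, and no observed control-site rate is reported.

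**The concern.** A controlled pre/post design exists to estimate how much more the intervention site changed from baseline than the control site did. The stated test and decision rule describe something else, namely whether the two groups differ. With one hospital per arm and no randomisation, a difference between groups is the standing difference between the hospitals plus any effect of audit and feedback. The intervention wards were picked for poor compliance at their own hospital, so equal starting rates cannot be presumed.

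A single intervention parameter also leaves open which intervention it measures. In year 2 the intervention site receives individual feedback, monthly unit-level feedback and surveys, and the control site has no surveys. In year 3 the intervention site receives unit-level feedback only, and surveys run at both sites. The Study timeline section says the control-site surveys are added "so that we can assess the effect that the surveys alone have on prescribing behavior and on responses to survey questions", so the authors themselves allow that surveys may shift the outcome.

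At stake is the main conclusion for both parts of objective 1.

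**Working it through.** **1. The plan's own figure.** Inputs from the 1a sample-size section: p1 = 0.36, p2 = 0.25, two-sided α = 0.05, power 80%, φ = 2 arcsine √p.

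- h = 1.287 − 1.047 = 0.2398.
- n per site = 2[(1.960 + 0.842)/0.2398]² = 273.
- Power at 300 = Φ(0.2398 × √150 − 1.960) = Φ(0.977) = 83.6%.
- The usual two-proportion formula with continuity correction gives 292.

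So 300 per site is adequate for the test it describes: one period, two groups, no baseline.

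**2. What the intervention parameter can mean under the listed terms.**

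| Coding | What the parameter estimates |
|---|---|
| Constant site indicator, ward terms not fixed | Hospital difference plus any effect |
| Constant site indicator, ward terms fixed | Not estimable, because wards are nested in sites |
| Indicator on only at the intervention site after year 1, wards fixed, no period term | Before/after change at the intervention site; control wards have no variation in the indicator and do not correct for time |

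In the third row, secular trend and the algorithm distribution that starts at both sites in year 2 enter the estimate. Every row needs period and site-by-period terms to recover the controlled contrast.

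**3. Size under a pure site contrast.** The gaps are assumptions, since no control-site rate is given. Formula: with d = |φ1 − φ2| × √(n/2) and n = 300 per site, the rejection probability is Φ(d − 1.960) + Φ(−d − 1.960).

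| Situation | Rates compared | Difference in φ | d | Rejects |
|---|---|---|---|---|
| No effect, 5-point standing gap | 36% v 31% | 0.1060 | 1.298 | 25% |
| No effect, 10-point standing gap | 36% v 26% | 0.2169 | 2.656 | 76% |
| True fall 36% to 25%, control already at 25% | 25% v 25% | 0 | 0 | 5% |

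In the first two rows the result is a false benefit if the control site is the higher one and apparent harm if it is the lower. In the third row half of the 5% lies in the wrong direction.

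**4. Power for the site-by-period contrast.** Assumed rates: 36% in both baseline cells and in the control follow-up cell, 25% in the intervention follow-up cell, independent episodes. Each cell contributes variance 1/n on the arcsine scale, so the contrast has variance 4/n instead of 2/n.

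- n per site per period = 4[(1.960 + 0.842)/0.2398]² = 546.
- Power at 300 = Φ(0.2398 × √75 − 1.960) = Φ(0.117) = 54.6%.
- On the risk-difference scale: 570 needed, 53% power at 300. On the logit scale: 526 needed, 56% power.

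**5. Objective 1b.** Inputs from its sample-size section: 1,867 and 1,512 patients a year, 10% reduced by a quarter to 7.5%, so h = 0.0887.

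- Single-period comparison: SE = √(1/1867 + 1/1512), power 73% two-sided (82% one-sided), against the stated 80%.
- Site-by-period, arcsine: SE = √(2/1867 + 2/1512) = 0.0489, power = Φ(1.813 − 1.960) = 44%.
- Site-by-period, risk difference: SE = √[0.09(2/1512 + 1/1867) + 0.0694/1867] = 0.0143, power = Φ(1.749 − 1.960) = 42%.

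**The case against.** The strongest reply is that the article is silent on coding rather than wrong. The design is called pre/post, Table 3 speaks of measuring change, and the text refers to a parameter for the intervention, not for the site. An indicator that is on only at the intervention site after year 1 fits those words. The listed ward terms, if fixed, would absorb a standing hospital difference. The unit-level analysis of covariance for culture and catheter-use rates might take the baseline rate as covariate.

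Part of this stands. A reader might infer that the baseline year is excluded from the tests, or that years 2 and 3 are pooled in one test. The documents say neither: they do not state which years enter, and they give the two years different purposes. Nor can one say outright that the site coefficient is biased by the hospital difference, because that depends on how the ward terms enter.

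It does not rescue the plan. The switch-on coding without a period term exchanges one confounder for another. Fixed ward terms make a constant site indicator inestimable. The covariance analysis names no covariate, compares units, and does not cover 1a. The decision sentence still describes a difference between groups. Leaving detail to a fuller plan does not settle the matter either, because the article does state the test, the covariates and how significance will be read.

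It is also fair that the standing gaps are hypothetical and that the sites were chosen as alike in organisation and patient population. That likeness is not evidence of equal rates of inappropriate treatment.

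**Conclusion.** The point holds: the stated tests, covariates, decision rule and sample size do not match the controlled pre/post design. Depending on the coding, the intervention parameter is confounded with the hospital difference, is not estimable, or is confounded with changes over time.

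The rejection rates of 25% and 76%, and the 5% detection rate, illustrate the pure site contrast only. They assume standing gaps of 5, 10 and 11 points, 300 episodes per site, and no covariates or clustering. They show what such gaps would do, not that they exist. The mismatch itself does not depend on those assumptions. Because it governs the main conclusion for 1a and 1b, it should be corrected before the data are analysed.

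**What to change.** Include the year-1 data and fit ward, period and site-by-period terms. Make site x year-2 (change from year 1, intervention v control) the primary test for 1a and 1b. Estimate site x year-3 separately, since the feedback and the survey exposure differ between the two years. Reword the decision sentence so that significance refers to the site x year-2 term. State that with one site per arm a hospital-specific event in year 2 cannot be separated from the intervention.

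No new kind of data is needed, because surveillance already covers both sites in all three years. The cost is precision, and the power statements for 1a and 1b must be restated for this contrast. Ignoring clustering, 1a has about 55% power at 300 episodes per site per period and needs about 546 for 80%; 1b at 10% v 7.5% has about 42% to 44%. Correlation within patients and providers would be expected to lower these further. The restated section should give the number of bacteriuria episodes expected per site per year, so that a reader can judge whether 546 is within reach.
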